### Study-wide number of subjects

We propose a maximum sample size of 90 infants. Five infants (three to receive *B. infantis* supplementation and two to receive placebo) will be enrolled for the initial dose of *B. infantis*. An additional five infants will be enrolled at each dose escalation. Once the pharmacologically effective dose (ED) of *B. infantis* has been reached, two additional dose escalations will be performed (for reasons as described above). We estimate that the ED of *B. infantis* will be identified within seven dose escalations (35 infants). Accounting for the final two dose escalations will bring the total to 45 infants. Following the final dose escalation, 45 additional infants (27 to receive *B. infantis* and 18 to receive placebo) will be enrolled to screen for lower-frequency adverse events using Hanley’s Rule of Three [21]. This will bring the maximum enrollment number to 90 infants. If the ED of *B. infantis* required to produce 50 % gut colonisation at 6 weeks is not reached, then enrollment will be halted after 90 infants have been enrolled. Additional stopping rules are listed in the “Study Endpoints” section.

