## Methods/Design

### Study design

The proposed phase I clinical trial is a parallel-group, placebo-controlled, randomised, double-blind ascending dose study of dietary supplementation with *B. infantis* in healthy breastfed infants to evaluate its safety as well as determine the ED of *B. infantis* producing >50 % gut colonisation at 6 weeks of age. Infants will be enrolled sequentially in groups of five (three randomised to receive *B. infantis* and two to receive placebo). The trial participants and investigators will be blinded as to their group randomisation, which will be conducted by the study pharmacist (who will then dispense blinded *B. infantis* or placebo to the investigators). Depending on group assignment, each infant will receive one dose of either *B. infantis* or placebo on day 7 and another on day 14 of life (two doses total). For infants in the *B. infantis* group, a calculated maximally recommended starting dose (MRSD) will be used to initiate the dose escalation and is defined below. Every 2 weeks, an additional group of five infants (randomised 3:2 to *B. infantis* and placebo) will be enrolled to receive progressively higher doses of *B. infantis*. Calculation of the appropriate dose escalation will be performed using a modified Fibonacci series as described below in an effort to identify the ED of *B. infantis*.

After the ED of *B. infantis* has been identified (defined as the dose capable of producing 50 % gut colonisation by 6 weeks of age) two additional sequential dose escalations will be performed. The purpose of the final two dose escalations is to determine if successively higher doses of *B. infantis* result in increased gut colonisation or barrier protection, or, alternatively, if a maximum effective dose (MaxED) for *B. infantis* exists above which there is no further increase in gut colonisation or barrier protection. Following the final dose escalation, Hanley’s Rule of Three will be applied in order to determine if lower-frequency adverse events are caused by *B. infantis*. Hanley’s Rule of Three states that in order to identify any adverse events occurring at a frequency of 1:10 or greater with a 95 % confidence interval, at least 30 subjects must be enrolled [21]. A schematic overview of the trial design and dose escalation protocol is provided in Fig. 1.

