### Rules for stopping dose escalation and halting trial

Dose escalation will be stopped if a maximally tolerated dose (MTD) of *B. infantis* is reached. The data safety monitoring board will evaluate the adverse events reported at each ascending dose of *B. infantis*. If the safety monitoring board deems that one or more of the three infants in the *B. infantis* supplementation group experienced an adverse event (such as fever >38.9 °C (102 °F), abdominal pain or colic, blood or purulence in the stool, diarrhoea or vomiting) then additional dose escalation will be halted.In the event dose escalation is halted due to adverse events, an additional group of five infants will be enrolled with three infants at the same (i.e. not escalated) dose of *B. infantis* and two receiving placebo.If no adverse events occur in this additional, non-escalated group, then dose escalation will be resumed beginning with the next group of enrolled infants.However, if adverse events are noted in one or more infant(s) in the non-escalated group, all further dose escalation will be halted. The *B. infantis* dose will be de-escalated to the previous value, and an additional group of five infants (three *B. infantis*, two placebo) will be enrolled. If no adverse events occur in the de-escalated group, this dose will be considered the MTD and the trial will be stopped.If any adverse events are noted in the de-escalated group, further de-escalation and enrollment of infants will occur to identify the dose of *B. infantis* considered to be the MTD, in which no adverse events occur in the study group.

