### Withdrawal of subjects

Subjects may be withdrawn without their consent if they acquire medical issues during the study period that require administration of oral or parenteral antibiotics or immunosuppressive medications. If a subject is to be withdrawn, the parent(s) will be contacted and the reason(s) for withdrawal will be explained in full. No further data will be collected from withdrawn subjects.

Subjects have the right to withdraw from the study at any time for any reason. Every effort will be made to follow-up subjects who discontinue placebo or *B. infantis* supplementation prior to the second dose. These evaluations should continue according to the protocol of scheduled study visits if at all possible. The reasons for discontinuation will be recorded in the subjects’ study file. If a subject is unable to return for evaluation, every effort will be made to contact via telephone 28 days after withdrawal to determine if any serious adverse events have occurred while off study. Any identified adverse events will be followed until resolution.

The investigator also has the right to remove subjects from the study without their consent. Possible reasons for removal include:Non-compliance with the study protocolSignificant protocol deviationSerious adverse event potentially related to study treatment

Subjects that withdraw after the 6 week study visit will not be replaced with new subjects.

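### The stated maximum of 90 infants is the size with no repeat groups; one clean repeat group on the full path takes enrolment to 95

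*Protocol article*

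**What the plan says.** The section *Study-wide number of subjects* of the protocol article opens with "We propose a maximum sample size of 90 infants" and then builds the figure. Five infants receive the initial dose level, and "An additional five infants will be enrolled at each dose escalation". The section expects the ED within seven escalations and counts these as 35 infants. Then "Accounting for the final two dose escalations will bring the total to 45 infants", and "Following the final dose escalation, 45 additional infants (27 to receive *B. infantis* and 18 to receive placebo) will be enrolled". The sum is given as 90. A halt at 90 is stated only for the case where the ED is not reached. The reader is referred to the additional stopping rules, but their infants are not counted.

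The section *Rules for stopping dose escalation and halting trial* sets those rules. If the safety board deems that at least one of the three active infants in a cohort had an adverse event, escalation is halted and "an additional group of five infants will be enrolled with three infants at the same (i.e. not escalated) dose". If this repeat group is clean, escalation resumes. If it is not, the dose goes down one step with another group of five, and a clean group there ends the trial.

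*Withdrawal of subjects* says only: "Subjects that withdraw after the 6 week study visit will not be replaced with new subjects". The caption of Fig. 1 requires 30 infants at the highest dose of *B. infantis*, to satisfy the rule of three.

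**The concern.** A figure called a maximum should cover every path that the same document lays down. The sum has no line for a repeat group, yet after a clean repeat group the rest of the design goes ahead in full. The repeat infants therefore come on top of the 90 whenever the ED is found as late as the sum assumes.

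The article does not say what gives way. If 90 is not enforced, enrolment passes the stated maximum. If it is enforced, the shortfall would naturally fall on the group enrolled last. That is the expansion, which supplies 27 of the 30 active infants behind the statement about adverse events at a frequency of 1:10.

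**Working it through.** **Inputs (protocol article)**
- Cohort of 5, split 3 active to 2 placebo: *Study design*.
- Seven cohorts to the ED (35 infants), two more (total 45), expansion of 27 + 18, stated maximum 90: *Study-wide number of subjects*.
- Trigger, repeat group, resumption, de-escalation and end of trial: *Rules for stopping dose escalation and halting trial*.
- 30 active infants at the highest dose: caption of Fig. 1.
- Per-infant adverse event rate p: not given, so a range is assumed.

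**1. The plan's own figure.** 7×5 + 2×5 + (27 + 18) = 35 + 10 + 45 = 90. It reproduces exactly. Active infants: 9×3 + 27 = 54. Placebo: 9×2 + 18 = 36. Active at the top dose: 3 + 27 = 30. No slack remains.

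**2. Clean repeat groups, ED at the seventh level.** With r repeat groups, each clean, N = 90 + 5r.
- r = 1: 95
- r = 2: 100
- r = 8 (every level below the top): 130
- r = 9: 135, if the top level is also repeated and the expansion still follows

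**3. ED found earlier, at level m.** Without repeats, N = 5(m + 2) + 45. This gives 85 at m = 6 (room for one extra group), 80 at m = 5 (two groups) and 60 at m = 1 (six groups).

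**4. De-escalation.** A clean de-escalated group ends the trial, so the 45 expansion infants are not enrolled. With k cohorts, one repeat group and j de-escalation steps, N = 5k + 5 + 5j. The largest case is k = 9, j = 8: 45 + 5 + 40 = 90. With all nine levels repeated and de-escalation after the ninth, N runs from 45 + 45 + 5 = 95 to 45 + 45 + 40 = 130.

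**5. How likely is N > 90 on the full path?** A cohort triggers with probability q = 1 − (1 − p)³. A level is passed, at once or after a clean repeat, with probability (1 − q) + q(1 − q) = 1 − q². All nine are passed with probability (1 − q²)⁹, and all nine without any repeat with probability (1 − q)⁹ = (1 − p)²⁷. The difference is the chance of completing all nine levels with at least one repeat.

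| Assumed p | q | All nine passed | No repeat | Passed with at least one repeat (N > 90) |
|---|---|---|---|---|
| 1% | 0.030 | 0.992 | 0.762 | 0.23 |
| 2% | 0.059 | 0.969 | 0.580 | 0.39 |
| 5% | 0.143 | 0.831 | 0.250 | 0.58 |
| 10% | 0.271 | 0.503 | 0.058 | 0.45 |
| 20% | 0.488 | 0.086 | 0.002 | 0.08 |

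This takes the ED at the seventh level, independent infants, the same p at every dose, every event counted by the board, and the ninth level handled like the others.

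**6. If 90 were held as a cap in this branch.** Each repeat below the top dose cuts the expansion by five, three of them active. The chance of seeing at least one event of frequency 1:10 among n infants is 1 − 0.9ⁿ, and the rule-of-three bound is 3/n.

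| Repeats below the top dose | Active at the top dose | Chance of seeing a 1:10 event | 3/n |
|---|---|---|---|
| 0 | 30 | 95.8% | 10.0% |
| 1 | 27 | 94.2% | 11.1% |
| 2 | 24 | 92.0% | 12.5% |
| 3 | 21 | 89.1% | 14.3% |

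A repeat at the top dose itself costs nothing on this count: 3 + 3 + 24 = 30.

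**The case against.** The strongest reply is that the sum is correct and that 90 fails as a maximum on one kind of path only: the ED comes as late as the seventh level and at least one repeat group is clean. Fig. 1 places the ED, for illustration, at Group 6, where the total is 85 and one repeat group still fits. The trigger also rests on the board's judgement and not on a simple count. All of this stands, but a stated maximum has to cover the late case, which is the case the section itself uses to reach 90.

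Several stronger readings are tempting and are not supported:
- A reader might infer that de-escalation groups also break the figure. After a single repeat group they do not, because the trial then stops without the expansion. De-escalation passes 90 only in combination with further repeats.
- A reader might take replacement of early withdrawals as prescribed. The article rules out replacement after the week 6 visit. Replacement before it is only implied.
- A reader might take the complement of (1 − p)²⁷, which is 75, 94 and 99.8% at p = 5, 10 and 20%, as the chance of exceeding 90. It is the chance of at least one trigger in nine cohorts and includes trials that stop early.
- A reader might count an initial dose plus seven escalations as 40 infants, which leads to 95 by another route. The section itself puts seven escalations at 35 infants, and the listed dose series has seven multiples including the first. This is loose wording, not a second sample size.
- A reader might conclude that the safety statement is lost. No passage cuts the expansion once the ED is reached, so the cap in step 6 is hypothetical, and one repeat under it lowers detection only from 95.8% to 94.2%.

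**Conclusion.** The point holds in limited form. Ninety is the enrolment with no repeat groups and the ED at the seventh level, and the protocol's own rule for clean repeat groups takes it to 95 or more. The excess is five infants per clean repeat, up to 130 with repeats at all eight levels below the top. The count rests on the documents alone. The chance of exceeding 90 rests on assumed event rates: it is highest, near 58%, at about 5% per infant, and falls at high rates because the trial then tends to stop early. This is an inconsistency that should be corrected before recruitment. It does not undermine the design.

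**What to change.** Reconcile *Study-wide number of subjects*, *Rules for stopping dose escalation and halting trial* and *Withdrawal of subjects* in one of two ways:
1. Call 90 the size with no repeat groups and no replacements, and give the maximum as 90 + 5 per clean repeat group, plus any replacements.
2. Declare 90 a cap in every branch, say which part of the trial is shortened when repeat groups use up places, and restate the rule-of-three figure for the number of infants that remains.

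In either case, say whether withdrawals before the week 6 visit are replaced and whether the expansion follows a clean repeat at the top level. Reword seven dose escalations as seven dose levels, so that the 35 infants match the text.

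The first option costs a less favourable headline number and the second a weaker safety statement when repeats occur. Both need a text change in the protocol and the ethics file. The article says that recruitment has not begun, so this can be done before any infant is enrolled.

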**Fig. 1 Fig1:**
[figure not shown]
A parallel-group, placebo-controlled, randomised, double-blind ascending dose phase I study of dietary supplementation with *B. infantis.* Groups of healthy infants will receive increasing doses of *B. infantis* until it comprises 50 % of their gut microbiota, defined as the pharmacologically effective dose (*ED*). This figure arbitrarily designates Group 6 as receiving the ED of *B. infantis*. After the ED has been reached, two additional dose escalations will occur to determine the impact that additional *B. infantis* has on the gut microbiota. To satisfy Hanley’s Rule of Three, 30 infants will receive the highest dose of *B. infantis*. “*X*” represents the maximum recommended starting dose (*MRSD*). A modified Fibonacci Series (X, 2X, 3X, …) is used to guide the dose escalations. *CFU* colony-forming units

Study visits will be scheduled for weeks 1, 2, 6, 24, 36, 52, and 78. Parents will complete surveys at each study visit to monitor the infants for potential adverse events associated with probiotic administration including feeding intolerance, fevers, or bowel irregularities including constipation and diarrhoea.

Stool samples will be collected twice weekly for the first 6 weeks of life then once weekly at weeks 24, 36, 52, and 78. Stool samples will be analysed to determine the relative abundance of *B. infantis* over time, and the overall diversity of the gut microbiota with and without *B. infantis* supplementation. Stools will also be analysed for milk oligosaccharides to verify consumption of breast milk and to correlate the proportion of human milk oligosaccharides and free sugar monomers seen in the infant stool at various levels of *B. infantis* colonisation.

Breast milk will be collected at 7, 14, 42, 120, and 180 days after the birth of the infant to determine the type and proportion of milk oligosaccharides present at various time points. The purpose of this analysis is to allow correlation of the type and amount of milk glycans present in breast milk with that in the infant stool samples.

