### Protocol for calculating the starting dose of *B. infantis* and dose escalation

Previous studies of *B. infantis* supplementation in premature infants at the UC Davis neonatal intensive care unit (NICU) have used a dose of 1.4 × 10^9^ colony-forming units twice daily for 2 weeks without any observed serious adverse effects [22]. Applying a safety factor of three and adjusting for once-daily dosing yields, a MSRD of 0.9 × 10^9^ colony-forming units of *B. infantis* is to be administered on day 7 and day 14 of life. Each group of five infants will be enrolled at least 2 weeks apart to allow for sufficient time to identify possible adverse events prior to each dose increase. A modified Fibonacci-based dose escalation protocol will be applied as shown below:$$ {F}_n={\displaystyle \sum_{k=0}^{\left[\frac{n-1}{2}\right]}}\left(\begin{array}{c}\hfill n-k-1\hfill \\ {}\hfill k\hfill \end{array}\right) $$

The specific modified-Fibonacci series will be as follows:

×, 2×, 3×, 5×, 9×, 12×, and 16× (where × = 0.9 × 10^9^ colony-forming units of *B. infantis*)

Based on the schedule for enrolling new groups every 2 weeks, by the time the pharmacologically effective dose (ED, defined as the dose of *B. infantis* resulting in 50 % gut colonisation at 6 weeks of age) has been identified, two additional dose escalations will have been performed in successive infant groups. Figure 1 provides schematic representation of infant group enrollment as well as the dose escalation protocol to identify the ED for *B. infantis* as well as the MaxED, if applicable.

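### The dose list has seven levels but the 45- and 90-infant totals need nine, so a late effective dose leaves later escalations and the safety expansion without a stated dose

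*Protocol article*

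**What the plan says.** Four places in the protocol article bear on the number of dose levels.

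- **Protocol for calculating the starting dose and dose escalation.** After displaying a Fibonacci sum, the text says "The specific modified-Fibonacci series will be as follows" and lists seven multiples of the starting dose (0.9 × 10^9 colony-forming units): 1, 2, 3, 5, 9, 12 and 16. The list ends there, with no ellipsis.
- **Study-wide number of subjects.** Five infants receive the initial dose level (three active, two placebo). Then "An additional five infants will be enrolled at each dose escalation". The authors estimate that the ED "will be identified within seven dose escalations (35 infants). Accounting for the final two dose escalations will bring the total to 45 infants". A further 45 infants (27 active, 18 placebo) follow the final escalation, giving a maximum of 90. If the ED "is not reached, then enrollment will be halted after 90 infants have been enrolled".
- **Study design.** The two escalations after the ED are meant to "determine if successively higher doses of" *B. infantis* add colonisation or barrier protection, or whether a maximum effective dose (MaxED) exists. They are therefore new levels above the ED, not repeats of it.
- **Fig. 1 caption.** "This figure arbitrarily designates Group 6 as receiving the ED of" *B. infantis*, followed by two more escalations. The caption writes the series as open-ended and gives the highest dose to 30 infants.

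**The concern.** In an ascending-dose trial the ladder of doses is the intervention, and the sample size is a count of rungs on it. Here the list and the count disagree: the enrolment totals budget for more levels than the list contains.

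Two parts of the design depend on the top of the ladder. The MaxED question is answered only by the two levels above the ED. The safety expansion, which carries the screen for lower-frequency adverse events, follows the final escalation. The dose section also says that, on the two-weekly enrolment schedule, the two further escalations will already have been made by the time the ED is identified. Doses for those levels are therefore needed before anyone knows where the ED lies.

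**Working it through.** **Inputs.** Five infants per level, three active and two placebo; seven levels to find the ED; two more levels; an expansion of 45, of whom 27 are active (all from Study-wide number of subjects). Seven listed multiples and one displayed formula (from the dose section).

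**Step 1: reproduce the plan's totals.**

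- 7 levels × 5 = 35.
- (7 + 2) levels × 5 = 45.
- 45 + 45 = 90.

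All three match, provided that seven escalations means seven levels including the starting dose. The literal reading, an initial level plus seven escalations, gives 8 × 5 = 40, then 10 × 5 = 50, then 95, and does not match. The plan's totals therefore rest on nine levels.

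**Step 2: compare with the list.** Levels listed: 7. Levels counted: 9. Levels 8 and 9 have no listed dose. The seven cannot already include the final two, because the totals would then be 7 × 5 = 35 escalation infants and 35 + 45 = 80 overall, not 45 and 90.

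**Step 3: when the gap opens.** The last level needed is the ED level plus 2.

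| ED at level | Last level needed | Levels with no listed dose | Escalation infants affected (active) |
|---|---|---|---|
| 1 to 5 | 3 to 7 | 0 | 0 |
| 6 | 8 | 1 | 5 (3) |
| 7 | 9 | 2 | 10 (6) |

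In the last two rows the final escalation has no listed dose, so the dose for the 45-infant expansion (27 active) is not stated either. In the worst case this is 10 + 45 = 55 of 90 infants, of whom 6 + 27 = 33 are active.

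**Step 4: can the displayed formula supply the missing levels?** F(n) is the sum over k, from 0 to the integer part of (n − 1)/2, of C(n − k − 1, k). Starting at n = 2 to line up with the list:

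| Level | 1 | 2 | 3 | 4 | 5 | 6 | 7 | 8 | 9 |
|---|---|---|---|---|---|---|---|---|---|
| Formula | 1 | 2 | 3 | 5 | 8 | 13 | 21 | 34 | 55 |
| List | 1 | 2 | 3 | 5 | 9 | 12 | 16 | none | none |

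For the fifth level, F(6) = C(5,0) + C(4,1) + C(3,2) = 1 + 4 + 3 = 8, against 9 in the list. The two differ from there on, so the formula does not extend the list.

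**Step 5: supporting points.** The Fig. 1 example implies 6 + 2 = 8 levels, one more than listed. If the ED is not reached within the seven listed levels (35 infants), the text does not say what is given between that point and the 90-infant cap.

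**The case against.** The best defence is that nine levels is a budget, not a commitment. The text only estimates that the ED will be found within seven levels, under a stated maximum. With the ED at level 5 or lower, the seven listed doses are enough. That is right, and it makes the gap conditional. It does not remove it, because the plan's own totals allow for an ED at level 6 or 7.

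A second defence is that a series called modified need not follow the plain Fibonacci values, so the explicit list governs. That also stands, and for the same reason the uneven step sizes break no stated rule and are not part of this point. But if the list governs, it stops at seven.

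A reader might infer more than the documents support:

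- *The plan commits to 18 levels, since 90/5 = 18.* It does not. The 90 is a ceiling, 45 of those infants are otherwise planned for the expansion, and the stopping rules provide for repeated and de-escalated groups that need no new dose. What happens in that branch is unclear, and no more can be said.
- *Fig. 1 proves that an eighth level has no dose.* The image could not be read here and may print doses by group, and the caption itself calls the choice of Group 6 arbitrary.
- *The ED cannot be identified beyond level 5.* It can be identified at level 6 or 7. What lacks a dose is one or both of the later escalations and the expansion.
- *Ten infants would receive an undefined active dose.* At 3:2 allocation, four of the ten are on placebo.

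It does not help that this is a condensed article. The article itself prints the list, the formula and the counts, and they disagree.

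**Conclusion.** The contradiction is firm: seven dose levels are listed and nine are counted, and the totals of 45 and 90 depend on nine. The list supports the ED plus two escalations only for an ED at level 5 or lower. For an ED at level 6 or 7, one or two escalation groups (5 or 10 infants, 3 or 6 of them active) and the safety expansion that follows have no dose in the readable text. Seven levels alone would give 35 and 80.

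This rests on three assumptions: five infants per level, seven escalations counted to include the starting dose (the only reading that gives 35), and no further doses printed in Fig. 1. If the figure does print doses beyond 16 times the starting dose, the text and the figure still need to agree.

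The point should be settled before the first infant is enrolled.

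**What to change.** Reconcile Study design, the Fig. 1 caption, the dose-escalation section and Study-wide number of subjects, so that four things agree: the number of dose levels, the list, the displayed formula and the enrolment counts 35, 45 and 90. Arithmetically there are two ways to agreement. Either the list covers every level that the counts assume, or the counts are restated to what seven levels support (35 escalation infants and 80 overall, with two further escalations available for an ED at level 5 or lower).

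The displayed formula should either reproduce the list or be removed. The text should also say what the plan provides when the listed series is exhausted, both when the ED is found late and when it is not found.

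Which doses belong on the ladder, and any escalation or stopping rule, are for the sponsor to decide. None is proposed here.

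The cost is amendment wording and, if needed, a corrected figure. Trial status says that recruitment has not begun, so no enrolled infant is affected.
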